## Abstract

**Background:**

Changing current dietary patterns into sustainable healthy diets (ie, healthy diets with low environmental impact and socioeconomic fairness) is urgent. So far, few eating behavior change interventions have addressed all the dimensions of sustainable healthy diets at once and used cutting-edge methods from the field of digital health behavior change.

**Objective:**

The primary objectives of this pilot study were to assess the feasibility and effectiveness of an individual behavior change intervention toward the adoption of a more environmentally sustainable healthy diet as a whole and changes in specific relevant food groups, food waste, and obtaining food from fair sources. The secondary objectives included the identification of mechanisms of action that potentially mediate the effect of the intervention on behaviors, identification of potential spillover effects and covariations among different food outcomes, and identification of the role of socioeconomic status in behavior changes.

**Methods:**

We will run a series of ABA n-of-1 trials over a year, with the first A phase corresponding to a 2-week baseline evaluation, the B phase to a 22-week intervention, and the second A phase to a 24-week postintervention follow-up. We plan to enroll 21 participants from low, middle, and high socioeconomic statuses, with 7 from each socioeconomic group. The intervention will involve sending text messages and providing brief individualized web-based feedback sessions based on regular app-based assessments of eating behavior. The text messages will contain brief educational messages on human health and the environmental and socioeconomic effects of dietary choices; motivational messages to encourage the adoption of sustainable healthy diets by participants, providing tips to achieve their own behavioral goals; or links to recipes. Both quantitative and qualitative data will be collected. Quantitative data (eg, on eating behaviors and motivation) will be collected through self-reported questionnaires on several weekly bursts spread through the study. Qualitative data will be collected through 3 individual semistructured interviews before the intervention period, at the end of the intervention period, and at the end of the study. Analyses will be performed at both the individual and group levels depending on the outcome and objective.

**Results:**

The first participants were recruited in October 2022. The final results are expected by October 2023.

**Conclusions:**

The results of this pilot study will be useful for designing future larger interventions on individual behavior change for sustainable healthy diets.

**International Registered Report Identifier (IRRID):**

PRR1-10.2196/41443

## Introduction

### Background

Sustainable healthy diets have been defined as healthy dietary patterns with low environmental impact and being economically fair and affordable and culturally acceptable, which contribute to nutrition security and a healthy life for the present and future generations [1]. Such diets are characterized by being nutritionally balanced patterns, mainly (if not totally) based on unprocessed or minimally processed plant-based foods obtained from fair sources and with minimal food waste [2]. Over the past decades, the way food has been produced and consumed is far from being healthy or sustainable: unhealthy diets are the leading cause of morbidity and mortality worldwide [3]; healthy diets are not affordable and accessible to a large proportion of the world’s population [4]; the current food system is among the main drivers of environmental pollution and natural resource use [5]; and from the socioeconomic and ethical perspectives, there are countless cases of forced labor conditions and unfair salaries across the food system [6]. Altogether, changing the current food system toward a sustainable and healthy one is timely. This mission requires large transformative changes in each food system phase, from production to consumption, and all stakeholders, from producers to consumers, should be involved in such a transformation [7].

To encourage the adoption of sustainable healthy diets, structural changes (ie, political actions or nudges) have to be combined with strategies explicitly tailored to individual behavior change [8,9]. To date, most individual eating behavior change interventions implemented have mainly focused on improving health and, to a lesser extent, on the dimensions of sustainable eating behaviors (ie, their environmental impacts and, with even less consideration in the literature, their social consequences [10]). Evaluating all these dimensions at once within interventions is crucial because they are not necessarily aligned. For instance, fish is a healthy food but could be obtained from overexploited fish stocks, exacerbating environmental damage [11]; even if captured from sustainable sources and using environmentally responsible techniques, labor conditions for fishery workers may not be fair, compromising their well-being [6].

### Prior Work

Recently, some interventions have been designed with the aim of promoting individual eating behavior change considering different dietary sustainability dimensions. For instance, O’Sullivan et al [12] have designed an intervention to encourage the adherence to a healthy diet with low environmental impact, but they have left aside other relevant behaviors to achieve a sustainable diet, such as food waste, and the socioeconomic consequences of dietary behaviors. An intervention implemented by Monroe et al [13] among US students has targeted food waste reduction and considered the social dimension of individual eating behaviors, such as promotion of the acquisition of local foods from farmers’ market. However, this intervention has not tackled the overall dietary pattern of the participants, focusing only on red meat consumption as the main outcome. Besides considering red meat reduction is key to transitioning to sustainable healthy diets, this approach lacks an assessment of the substitution effect and possibility of other changes in untargeted food groups (ie, spillovers), which could offset the overall effect of the intervention [14]. For example, if pork meat is replaced by hard cheese (one of the food products with the highest environmental impact), the dietary environmental impact would increase [15]. Therefore, eating behavior change interventions aimed at promoting sustainable healthy diets as a whole, that is, as a complex interplay of behaviors, are needed [16].

Beyond interventional studies, reviews have documented potential mechanisms of action that motivate or impede behavior change for a healthy and sustainable diet. A diversity of personal and interpersonal factors have been highlighted, such as sociodemographic determinants (ie, gender, age, socioeconomic level, and political orientation), food-related factors (ie, healthiness, taste, and affordability), generic motivational factors (ie, self-efficacy and habit), and specific motives for sustainability (ie, environmental impact, ecoanxiety, and social justice) [17-21]. By contrast, specific barriers have been identified, such as perceiving sustainable healthy food as less tasty [19]. These previous findings are useful for designing interventions (as levers to manipulate and be considered during a study) and for understanding the mechanisms of action that potentially mediate the effect of an intervention on behavior change.

At the methodological level, specific limitations of previous eating and proenvironmental behavior change interventions have also been repeatedly mentioned in the literature. They include the use of long, paper-based food frequency questionnaires that do not allow for frequent and dynamic assessment of the behavior change process [22], short or nonexisting follow-up periods that preclude the appreciation of long-term changes and potential forms of behavioral maintenance over time, and study designs inappropriate for testing causal relationships [23]. To build upon previous research, this pilot trial has been designed to promote individual behavior change for a sustainable healthy diet over a year with measurement bursts of daily eating behaviors digitally implemented through smartphones to better understand and monitor the behavior change process through the study [24].

The primary objectives of this study are as follows:

1.1 To evaluate the effectiveness of a pilot digital behavior change intervention promoting a more environmentally sustainable healthy diet (1.1.a) and relevant specific food outcomes related to dietary sustainability (1.1.b)

By sustainable healthy diet, we refer to a healthy dietary pattern with low environmental impact (objective 1.1.a), that is, incentivizing the consumption of fruits; vegetables; legumes; nuts; whole grains instead of their refined versions; unsaturated and nonrefined vegetable oils as main dietary fats; and water as the main beverage instead of others, such as sodas or alcoholic drinks, while promoting a reduction in the consumption of meat (especially red and processed meats), dairy products (especially cheese), sugar-added products, products high in salt, and ultraprocessed foods [25], with minimal food waste and the purchase of food from fair and ethical sources.

Specific food groups or relevant food-related outcomes that will be investigated closely (objective 1.1.b) include: the consumption of red and processed meat, fruits and vegetables, ultraprocessed foods, and dairy products, and food waste.

1.2 To examine the feasibility and acceptability of the intervention and collect relevant information for iteratively improving future interventions

The secondary objectives are as follows:

2.1. The identification of mechanisms of action, notably motivational ones, potentially mediating the effect of the intervention on behaviors

2.2. The identification of potential spillover effects and covariations among different food groups (eg, meat, fruits and vegetables, and ultraprocessed food) and dietary outcomes (ie, diet composition and food waste) occurring over the study

2.3. The identification of potential interaction effects between socioeconomic status and intervention effects on behaviors

## Methods

### Participants

Potential participants will be approached on the web via email and social media with the support of our institutional communication and outreach activities team (ie, Barcelona Institute for Global Health, ISGlobal). They will be invited to visit a website with a brief description of the study, which will contain a link to a Google form (Google LLC) with questions related to our inclusion and exclusion criteria (provided subsequently) that is to be completed by those interested in participating. Those meeting the inclusion criteria will be classified in 3 groups according to their subjective socioeconomic level. The reason behind this stratification is that socioeconomic level is a major determinant of food choices and individual dietary carbon footprints [26,27]. In addition, deprived populations might benefit less from interventions delivered via digital or mobile means; therefore, it is necessary to include social inequality indicators such as socioeconomic status in the evaluation of interventions to assess their potential differential impact [28,29]. We chose a subjective measure of socioeconomic level and status because it has been shown that socioeconomic status has an impact on how individuals perceive resources beyond their factual resources [30]. This indicator is also strongly associated with physical functioning and health outcomes, beyond objective measurements of socioeconomical level [31]. The MacArthur Scale of Subjective Social Status will be used [32]. This scale ranges from 1 (“perception of low social status”) to 10 (“perception of high social status”). In our study, participants scoring themselves from 1 to 3, 4 to 7, and 8 to 10 will form groups of low, moderate, and high socioeconomic statuses, respectively. Within each group, the first 7 participants meeting the inclusion criteria will be invited to participate in the study after stratification by gender, with the aim of having a balanced number of individuals identifying themselves as women and men in each group. In total, we aim to include 21 participants. The questionnaire used for checking the inclusion and exclusion criteria is provided in Multimedia Appendix 1.

Individuals will be enrolled in the study if they meet the following characteristics: adults aged from 18 to 65 years; residing in Barcelona; speaking and reading Spanish fluently; having a mobile phone supporting the installation of a smartphone app; reporting no history of eating disorders (eg, anorexia nervosa, bulimia nervosa, and binge eating) or any food intolerance or allergy (eg, celiac disease, and nut allergy) or other chronic illnesses that might directly impact eating behaviors (eg, diabetes, cardiovascular disease, cancer, and obesity); following an omnivorous diet; and scoring ≥5 out of 10 points on the dietary questionnaire included in the Google form (refer to Multimedia Appendix 2 for the scoring criteria). The exclusion criteria are being pregnant or planning to be pregnant in the next year, being in a postnatal situation for <3 months, breastfeeding, being professional athletes, following specific diets (eg, vegan, vegetarian, high protein, slimming, gluten free, and low in sugars), reporting any illnesses that might directly impact eating behaviors, and not taking their own decisions about food choices (eg, someone else, such as husband or wife or partner or mother or father, selects what they eat for most of their meals).

Participants will receive financial incentives for their participation. Over the course of the study, there will be 15 evaluation weeks, during which some questions should be answered daily and others once a week (refer to *Measurement* section). For each evaluation week, they will receive €10 (US $10.7) if they complete at least 6 out of the 7 daily questionnaires plus the weekly assessment. Thus, in total, each participant can receive €150 (US $160.4) for full participation in the study. At the end of the study, they will receive their money through bank transfer.

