### Data Analyses

#### Sample Size and Power Analyses for the Quantitative Side of the Project

The sample size for this pilot study is constrained by financial and human resources. We plan to recruit a total of 21 participants, with 7 participants in each subjective socioeconomic group (refer to the *Participants* section). However, in terms of statistical power, we will benefit from the intensive longitudinal nature of the study, that is, 15 evaluation weeks and up to 105 daily observations per participant. For objective 1.1.a, for which a weekly environmentally sustainable healthy diet index will be used, up to 315 observations will be available in total (21 participants × 15 evaluation weeks) and 105 observations per socioeconomic group (7 participants × 15 evaluation weeks). For objective 1.1.b, for which the daily raw data will be used, up to 2205 observations will be available in total (21 participants × 105 daily assessments), 735 observations in the 3 socioeconomic groups (7 participants × 105 daily assessments), and 105 observations at the individual level (as a general rule of thumb, a minimum of 70 observations are required for conducting individual-level analyses [48]). Given the pilot nature of this trial, we conducted power simulation analyses only for objective 1.1.a (ie, change in the weekly level of food healthiness and environmental sustainability). Considering group-level analyses and the analytical strategy detailed in the next section and assuming an increase of 2 units in the environmentally sustainable healthy diet score per phase, simulated power analysis indicated an adequate power value of 96%. The simulation was performed by generating the response variable as follows:

Fixed effects: the intercept was set at 6, and the fixed coefficient for the phase was set as −2 for the initial phase and +2 for the final phase based on our average expected change in the main outcome.Random effects: it was assumed that each participant would have both a random slope and a random intercept and that both followed normal distributions, with SDs of 2 for the intercept and 0.5 for the slope. The correlation between them was set as 0.2. The random effect for each participant was created by drawing random numbers from a multivariate normal distribution whose covariance matrix was specified using these parameters (R mvrnorm from the package *MASS*).

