##### Objective 1.1.a: Changes in the Environmental Sustainability and Healthiness of Diet

To test the main effect of the intervention on the environmental sustainability and healthiness of diet at the group level, linear mixed regression will be performed and expressed as measurement occasions (here, going from 1, first evaluation week, to 15, last evaluation week), using an ordered 3-categories phase variable as a fixed effect, which takes the values of baseline, intervention, and follow-up. Polynomial functions will also be fitted to the time variable to determine whether the index demonstrates any nonlinear patterns across time. If nonlinear patterns are detected, then other patterns (eg, quadratic, cubic, and piecewise) will be examined and selected based on visual inspections and goodness-of-fit indicators. Moderation analysis will be performed by exploring the role of the subjective socioeconomic level (ie, 3 socioeconomic groups entered as fixed effect) with regard to changes in diet. Fixed baseline characteristics will be included as control variables (ie, age, gender, education, income, and political orientation). Individual trajectories will be plotted, and heterogeneity in participants’ responses to the intervention will be discussed based on visual analyses using relevant guidelines for n-of-1 trials [50] (individual weekly changes in the whole diet will not be statistically modeled because only 15 observations will be available per participant).

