##### Objective 2.3: Potential Interaction of Socioeconomic Status With the Intervention Effectiveness

As mentioned in the previous sections, the role of socioeconomic status will be explored in objectives 1.1.a, 1.1.b, 2.1, and 2.2 by conducting group-specific analyses for the low, moderate, and high socioeconomic groups (refer to the above-mentioned sections for further details).

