## Discussion

### Principal Findings

With regard to objective 1.1.a, we expect environmentally sustainable healthy diet to positively change over time (increasing score for the environmentally sustainable healthy diet index) with small to medium effect sizes, as observed in most previous behavior change interventions [14]. With regard to objective 1.1.b, which focuses on food groups and food waste and reflects the changes in the index, we expect the consumption of meat, dairy products, and ultraprocessed food to decrease over time and the consumption of unprocessed or minimally processed plant-based foods to increase. However, the rate of change might differ from one food group to another; for example, an increase in fruit and vegetable consumption might occur earlier in the intervention than a decrease in meat consumption, which might indicate that this second behavior is more difficult to change. At the individual level, we also expect the shape of those changes to be heterogeneous across participants, with linear improvements, 1-step changes, and inverse U–shape, for example. Objective 1.2 (feasibility of the study) is not hypothesis driven.

With regard to objective 2.1, we expect substantial mediation effects of motivations, ecoanxiety, habit, and self-efficacy on eating behaviors, with positive changes in eating behaviors being partially explained by positive changes in these variables. More specific hypotheses can also be formulated; for example, we expect motivation for protecting the environment to mediate changes in the food groups with the highest environmental impact (eg, meat) more than those in the food groups mainly relevant for health (eg, ultraprocessed food).

We do not have clear and specific hypotheses regarding the covariations among food groups and among dietary outcomes (objective 2.2) and hypotheses regarding the moderating role of participants’ socioeconomic level (objective 2.3), given that only a few studies have examined these dimensions before; overall, the participants from the lowest socioeconomic group may present a less healthy and environmentally sustainable diet than the participants belonging to the higher socioeconomic groups [27,58].

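### Objective 2.3 asks for an interaction between socioeconomic status and the intervention effect, but the planned group analyses name no test of it and never use the recorded 1–10 ladder score

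*Protocol article*

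**What the plan says.** All references are to the protocol article.

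- **The objective.** The list of secondary objectives that closes the Introduction gives 2.3 as: "The identification of potential interaction effects between socioeconomic status and intervention effects on behaviors".
- **The moderator as measured.** Under Participants: "The MacArthur Scale of Subjective Social Status will be used". It runs from 1 to 10.
- **The moderator as analysed.** The same section bands it: "participants scoring themselves from 1 to 3, 4 to 7, and 8 to 10 will form groups of low, moderate, and high socioeconomic statuses". Recruitment follows the bands: "Within each group, the first 7 participants meeting the inclusion criteria will be invited to participate in the study after stratification by gender". The sample size section confirms 21 people, "with 7 participants in each subjective socioeconomic group".
- **The analysis for objective 1.1.a.** A moderation analysis is announced, with "3 socioeconomic groups entered as fixed effect". The section for 1.1.b says its strategy is similar.
- **The analysis for objective 2.3.** Status is to be explored across objectives 1.1.a, 1.1.b, 2.1 and 2.2 by "conducting group-specific analyses for the low, moderate, and high socioeconomic groups".
- **Expected shape.** Under Principal Findings the authors say that they have no clear and specific "hypotheses regarding the moderating role of participants’ socioeconomic level (objective 2.3), given that only a few studies have examined these dimensions before".

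**The concern.** An interaction is a statement about a difference between effects. Separate models in three groups give three effects, each with its own interval, but no estimate or test of how far they differ. A reader is then left to compare one group's significant result with another's non-significant one, which is not a valid comparison. Entering the groups as a fixed effect shifts each group's average level of the index. Only a product of group and phase lets the change between phases depend on group. The 1.1.a section uses the word moderation, so a product term may be intended, but it is not named, and the 2.3 section describes group-specific analyses only.

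The second part is efficiency. The ladder score is in hand for every participant, yet no described analysis uses it. Objective 2.3 rests on variation between 21 people, so it is a weakly informed question, and one ordered term is an economical way to ask it if the pattern is ordered.

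**Working it through.** **1. The plan's own figures.** No power is stated for objective 2.3. The only power figure, 96%, is for the phase effect in 1.1.a. It can be neither confirmed nor refuted, because the residual SD is not given. The observation counts reproduce: 21 × 15 = 315, 7 × 15 = 105, 21 × 105 = 2205, 7 × 105 = 735. They do not help here: status varies only between people, so moderation has 21 independent units however many days each contributes.

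**2. What separate group analyses deliver.** Let SD be the standard deviation, between people, of the individual phase effect. Each group estimate has standard error SD/√7 = 0.378 SD. The difference between two groups has standard error SD × √(2/7) = 0.535 SD, which is √2 times larger. The three separate models never compute that difference.

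**3. How much the bands discard.** Assume scores are uniform within bands and there are 7 people per band.
- Band means are 2, 5.5 and 9. Between-band variance = (3.5² + 0 + 3.5²)/3 = 8.167.
- Within-band variances are 0.667, 1.25 and 0.667, with mean 0.861.
- Share kept by the bands = 8.167/(8.167 + 0.861) = 90.5%.

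**4. Power under linear moderation.** Let d be the difference in individual effect over 7 rungs (band mean 2 to band mean 9), in SD units. Tests are two-sided at 5% on one change score per person.
- Ladder term, F on 1 and 19 df: noncentrality = 21 × 9.028 × d²/49. For d = 1 this is 3.87.
- Three-group test, F on 2 and 18 df: the group means are −d/2, 0 and d/2, so noncentrality = 7 × d²/2, divided by 1 + 0.861 × d²/49 for the spread left within bands. For d = 1: 3.5/1.0176 = 3.44.
- Trend over the three bands, F on 1 and 19 df: approximately the same 3.44 on one df.

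| d (SD) | Ladder, 1 df | Three groups, 2 df | Trend over bands, 1 df |
|---|---|---|---|
| 0.5 | 15% | 11% | 14% |
| 1.0 | 46% | 31% | 42% |
| 1.5 | 80% | 61% | 74% |
| 2.0 | 96% | 85% | 93% |

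Simulation agrees to within about two percentage points. At 1 SD the gain from 31% to 46% splits into 11 points from using one trend term (31% to 42%) and 4 points from using the full score (42% to 46%). If scores cluster near the cut points, all values fall: 64% (ladder) against 46% (three groups) at 1.5 SD, and 87% against 72% at 2 SD.

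**5. Power when moderation is not linear.** Simulation, 20,000 trials per setting, uniform scores.

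| Pattern | d (SD) | Ladder | Three groups |
|---|---|---|---|
| Only the low band differs | 1.0 | 38% | 41% |
| Only the low band differs | 1.5 | 66% | 76% |
| Only the middle band differs | 1.0 | 3% | 41% |
| Only the middle band differs | 1.5 | 2% | 77% |

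**6. On the index scale.** The documents do not give the SD of individual change, so it is an assumption. For a linear difference of 1 index point from low to high, the ladder against three-group power is 75% against 57% if the SD is 0.7, 46% against 31% if it is 1.0, 24% against 16% if it is 1.5, and 13% against 10% if it is 2.25.

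**The case against.** The bands are prespecified recruitment strata, so analysing and reporting by them is normal. Objective 2.3 is secondary and exploratory in a self-described pilot, no power is claimed for it, and no shape of moderation is predicted. The one directional remark, under Participants, is that deprived people may benefit less from digital delivery. That is compatible with a low band that differs from the rest, where the three-group test does better. The model details of an exploratory moderator are often left to a statistical analysis plan, which is not shown here.

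Most of this stands. A reader might infer that cutting the ladder wastes information and power outright, or that the ladder should replace the groups as the main moderation analysis. The documents support neither inference. The bands keep about 90% of the score variance, the advantage of the ladder needs a roughly linear pattern, and with no stated shape the three-group test protects against patterns that a linear term would miss almost entirely.

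What does not fall away is the mismatch. The article does not leave the method open: it states that an interaction objective will be met by group-specific analyses. Those do not answer it, whatever the pilot's size.

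**Conclusion.** The point holds as a modest, inexpensive improvement. As written, the analyses for objective 2.3 do not test the interaction that the objective names, and the recorded ladder score goes unused. Under roughly linear moderation a phase × ladder term would raise power by about 4 percentage points at 0.5 SD, 15 at 1 SD, 19 at 1.5 SD and 11 at 2 SD over a three-group test, mainly because it spends one degree of freedom instead of two. Under a low-band threshold or a middle-band pattern the three-group test is stronger. For differences of 1 SD or less, neither reaches 50% with 21 people, so no choice of test makes this an adequately powered question.

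These figures assume 7 completers per band, scores uniform within bands, equal variance of individual change across groups, one change score per person, and two-sided 5% tests. They say nothing against objective 1.1.a itself, nor against showing results by group.

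**What to change.** In the Objective 2.3 section, and by reference in 1.1.a and 1.1.b, state that moderation will be examined in models that include all 21 participants, with the participant random effects already planned:

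- one with a phase × ladder score term (1–10, continuous), alongside the main effects of both;
- one with a formal phase × group term (three levels), tested jointly.

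Report both with interval estimates, and label both as exploratory. Keep the group-specific results as descriptive estimates with plots, and keep the bands for recruitment. In the 1.1.a section, name the phase × group product explicitly, so that moderation is not read as a main effect of group. The subgroup mediation (2.1) and network (2.2) analyses are not replaced by this and can remain descriptive.

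The cost is wording plus one extra model per outcome. The downside is one more exploratory test, so neither interaction result should be singled out after the fact. No change to recruitment, measurement or sample size is needed.
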